## Abstract

**Background**

‘Open Dialogue’ is a social network model of crisis and continuing mental healthcare which involves elements of service delivery such as immediate response and a style of therapeutic meeting called network meetings. Although there are indications from non-randomised studies that it may help people in their recovery from severe mental health crises and improve long-term outcomes, this has yet to be tested in a randomised controlled trial.

**Methods**

This paper outlines the protocol for a multi-site cluster-randomised control trial assessing the clinical and cost-effectiveness of Open Dialogue compared to treatment as usual (TAU) for individuals presenting in crisis to six mental health services in England. The primary outcome is time to relapse, with secondary outcomes including measures of recovery and service use. Participants will be followed-up for two years, with data collected from electronic medical records and researcher-led interviews. The analysis will compare outcomes between treatment groups as well as investigating potential mediators of effect: shared decision-making and social network quality and size. Carers of a subsample of participants will be asked about their experiences of shared decision-making, carer burden, and satisfaction.

**Discussion**

This trial will provide evidence of whether Open Dialogue services implemented in the English mental health system is an effective alternative to current care and may have important implications for the organization of community mental health services.

**Trial registration**: retrospectively registered (108 participants recruited of 570 target) on 20/12/2019, ISRCTN52653325.

## Introduction

1

Mental health conditions often involve notable changes in behaviour, thinking and emotion associated with distress, functional impairment and reduced quality of life [4,21,57]. A mental health crisis in this study is defined as a mental health emergency, requiring an urgent response arising from a high risk of harm to self or others or a rapid increase in symptoms of psychosis or severe mood disorder, and which have a significant impact on personal or social functioning.

Those experiencing a mental health ‘crisis’, who are deemed to be at immediate risk to themselves (including suicide) or others or whose symptoms are rapidly worsening often require urgent specialist mental health support [53]. In the English system of state-funded healthcare, there are functionally distinct teams for treating those whose mental health needs are greater than can be met by primary care services [38]. Prompt access to care for those experiencing a crisis may lead to better long-term outcomes and reduced relapse [13,35]. In the English mental health care system this led to the development of Crisis and Home Treatment Teams [31] to provide short-term, intensive support as an alternative to hospital admission, alongside Community Mental Health Teams [17] which could provide long-term care if needed.

However, the need to move between different services during what can be an isolating and disturbing experience for an individual and their family and carers [23,47] has been criticised, with service-users reporting dissatisfaction with the quality of care they have received in the current system [9,26,37]. Given that on-going relationships with professionals has been identified as fundamental to recovery for service users [14,52], it is not surprising that disruptions to continuity of care may result in poorer mental health outcomes [34,52]. Furthermore, there are questions around the effectiveness of these distinct teams and whether they are able to meet their specific functions, with a recent survey finding only 19% of service users reporting a ‘very good’ experience with their community mental health team [10] and mixed evidence on whether crisis teams reduce the need for hospital admissions [28,29].

Open Dialogue is a person-centred, social network model of crisis and continuing mental healthcare where continuity of care is a key organisational principle [48]. It is both a therapeutic practice and a way of organizing a mental health service, and follows seven principles such as ‘immediate help’ and ‘psychological continuity’ [56]. The central means of intervention delivery is through ‘network meetings’: conversations between the service user, those important to them (such as family, formal and informal carers, and friends), and typically two Open Dialogue practitioners who remain with the same network throughout an episode of care [1]. These meetings encourage a shared understanding of the problems leading to a person's contact with the service and shared decision-making about any pharmacological, psychological, or social interventions [56]. It is suggested that this may increase feelings of agency, and the ability to develop and maintain mutual supportive relationships in the longer term [56].

Non-randomised studies have suggested that Open Dialogue may be associated with better mental health outcomes and reduced hospital admissions, ([22,56,50]. However, there is not yet the high-quality evidence for the clinical or cost effectiveness of Open Dialogue to support its widespread implementation [20]. This paper presents the design of and methods for a pragmatic cluster randomised controlled trial, which seeks to provide this evidence for Open Dialogue teams implemented in the English National Health Service (NHS).

## Trial design

2

This is a multi-site, two-arm, cluster randomised (1:1) controlled trial examining whether Open Dialogue is more clinically and cost effective than treatment as usual (TAU). It forms part of the ODDESSI (Open Dialogue: Development and Evaluation of a Social Network Intervention for Severe Mental Illness) research programme, which also includes development work, a feasibility trial, and a process evaluation.

### Objectives

2.1

Primary objective: To examine whether Open Dialogue is more effective than TAU at increasing time to relapse after recovery.

Secondary objectives: To examine whether Open Dialogue is more effective than TAU at:-Reducing time to initial recovery, increasing overall days spent in recovery, and increasing service-user defined recovery-Reducing service use and societal costs and improving health-related quality of life-Increasing service-users' satisfaction with care

We will examine whether social network quality, social network size or shared decision-making mediate the impact on the primary outcome. Additionally, we will examine the experience of carer burden, shared decision-making, and satisfaction with care for the family/carers of a subsample of trial participants offered Open Dialogue or TAU.

### Study setting and timeline

2.2

The trial takes place in six mental health services from inner and outer London, a large university town in the southeast of England and the surrounding suburban and rural communities, and a large costal conurbation in the south-west of England and its surrounding rural communities. The populations served vary considerably in the degree of social deprivation, available community resources and the structure of local mental health services. To commence recruitment, services must meet adequate fidelity to the model of care (see ‘monitoring intervention delivery’).

Participant recruitment commenced in the first site in June 2019, and all other sites were able to open to recruitment by January 2020. The protocol was registered during this set-up period (in December 2019). Recruitment was suspended in March 2020 (to reduce pressure on health services in the initial months of the COVID-19 pandemic) and restarted across the six sites from August 2020 to December 2020. Recruitment will stop in December 2021, the primary outcome will be available from December 2023, and data analysis will commence in early 2024.

### Trial clusters and randomisation

2.3

Trial clusters are defined in relation to groups of general practices (clinics where family physicians see patients). Inclusion criteria are as follows:•Each cluster must consist of two to four geographically co-terminous general practices (their catchment areas share a geographical boundary). There must be a clear and pre-existing shared referral pathway to a community mental health service, and a total of 65–75 patients per year referred to mental health crisis services.•Each general practice within the cluster should refer only within the catchment area of the community mental health service, refer at least 10 people per year to mental health crisis services, and have 2000 or more patients registered with the practice.

Once a mental health service has been recruited, GP practices within its catchment area are assessed and grouped into clusters in line with the cluster eligibility criteria. Relevant details of all the clusters from each catchment area are then sent to the trial statistician who randomly allocates in a 1:1 ratio to Open Dialogue or TAU. Cluster randomisation is stratified by catchment area of the local mental health services and restricted randomisation [11] is used to balance two continuous aggregated cluster-level covariates ‘average GP list size’ and ‘average IMD deprivation rate 2015’ [46] across the two trial arms and the strata. Where there are changes to general practices that form the basis of clusters (for example, two initially separate general practices merging to form a single practice) after cluster allocation, we aim to preserve selection of participants from the original clusters as far as possible.

### Participants' eligibility criteria

2.4

Participants who present to one of the participating mental health services who meet criteria for the crisis and continuing care pathway, and who are registered with a GP within a trial cluster are provided with Open Dialogue or TAU depending on their cluster. They may present by any route permitted within the service's local policies and procedures (for example, referral by a GP, an Emergency Department or other specialist service, or admission into an inpatient ward). There are further eligibility criteria for research participation:•Evidence of a mental health crisis indicated by (a) a rating of A-C on the UK Mental Health Triage Scale [53], which indicates either an emergency, very urgent or urgent response is needed based on a high risk of harm self or others and/or rapidly increasing symptoms of psychosis or severe mood disorder**,** (b) an admission to an inpatient ward or (c) being accepted into the care of a mental health crisis service•18 years of age or more•Sufficient English language abilities to participate in the research

Exclusion criteria are as follows: a diagnosis of dementia or an acquired cognitive impairment, a primary diagnosis of a learning disability or substance misuse, having no fixed abode, being under the care of forensic mental health services, and having previously received Open Dialogue.

Recruitment to the study was also not possible for those who are already participating in another research project that may impact their care in this trial, or if recruitment to the study would pose a risk of harm to the participant, study clinicians, or researchers.

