## Intervention delivery

3

Open Dialogue teams offer care from initial presentation in crisis through to discharge from the service, typically through ‘network meetings’ which include the service user, people they identify as important to them such as family members, and two or more Open Dialogue Practitioners. The agenda is set by the network, and there is a strong emphasis on service-user participation in any treatment decisions. Wherever possible, the same practitioners remain with the network throughout. Teams are multidisciplinary, typically including nurses, social workers, peer practitioners, clinical psychologists, occupational therapists, and psychiatrists, all of whom have undertaken an Open Dialogue training programme. Services are underpinned by the seven key principles of Open Dialogue: (1) Immediate Help; (2) A Social Network Perspective; (3) Flexibility and Mobility; (4) Responsibility; (5) Psychological Continuity; (6) Tolerance of Uncertainty; and (7) Dialogue and Polyphony [56]. They are ‘needs-adapted’ and network meetings take place as little or often as required by the network, perhaps occurring twice weekly in the time immediately after referral, moving to weekly or fortnightly as treatment progresses, whilst also working flexibly in collaboration with other services [48]. There is an ‘open discharge policy’, with service users able to ask for further network meetings at any point after discharge from the service, ideally with the same practitioners.

TAU is current routine crisis care and continuing community care, as delivered by English mental health services. This is based on a model which comprises a number of multi-disciplinary teams, the provision of care coordination, and a range of community and in-patient interventions and support.

 Participants in both trial arms may be offered any intervention they would ordinarily have access to individual psychological and pharmacological interventions, social, and housing support. The duration of contact is determined by each team, based on clinical need. Those with complex problems may receive continuing care for the duration of the study. Open Dialogue is not offered to those in the TAU arm. The provision of mental health services after the follow-up period has ended will be the responsibility of the participants' current mental healthcare provider.

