### Monitoring intervention delivery

3.1

The fidelity of service delivery in both the Open Dialogue and TAU teams is assessed to ensure that that the core structural components of services are delivered as intended. The ODDESSI fidelity measure [3] draws on an existing measure [44], and is based on interviews with service staff and review of documentation. Four key aspects of service functioning are rated: (1) Team structure and culture, (2) Access and engagement, (3) Delivery of care, (4) External support. To meet fidelity services must score at least 2.4 of 4 on each of the above.

The extent the core therapeutic components of Open Dialogue are delivered within a network meeting is measured using the Open Dialogue Adherence scale [32] which was developed from (and closely aligned with) a previous adherence measure [44]. Audio recordings are assessed by trained raters and scored according to the key elements of dialogic practice [32,43] and then rated as ‘acceptable’ or ‘unacceptable’. In ‘acceptable’ tapes at least two thirds of statements used by practitioners are dialogic (rather than monologic) and less than two statements are patronizing or disrespectful, and at least 10 out of 12 of the items based on the key elements of dialogic practice score ‘acceptable’.

All Open Dialogue and TAU teams are monitored prior to participant recruitment and at 6-monthly intervals throughout intervention delivery. Where fidelity or adherence is identified as falling below the pre-determined levels, remedial action is taken, and recruitment may be stopped locally in that cluster if the problem persists despite remedial action. Actual intervention or ‘dose’ received: the number, date, and mode of delivery of clinical meetings, is also recorded at a participant level.

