#### Baseline and follow-up research interviews

4.2.1

The baseline timepoint is the date of the crisis referral. This referral takes place after cluster randomisation, but before a potential participant has been assessed as meeting eligibility criteria prior to consent. The first research interview is conducted as close as possible to the date of the crisis referral (baseline) after consent is provided. Research interviews either occur in person (i.e. at the research site or at participant's homes) or over the telephone (the primary method of data collection during the COVID-19 pandemic). Follow-up interviews are undertaken at 3, 6, 12, and 24 months from baseline (see Fig. 1).

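### The exclusion for earlier receipt of Open Dialogue acts after allocation and almost entirely in one arm, and could bias the primary hazard ratio

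*Protocol article*

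**What the plan says.** Section 2.4 (Participants' eligibility criteria) sets out two layers. Care comes first: people who meet the pathway criteria and are "registered with a GP within a trial cluster are provided with Open Dialogue or TAU depending on their cluster". Research eligibility is a further layer, and its exclusions include "being under the care of forensic mental health services, and having previously received Open Dialogue". No time limit is attached to earlier Open Dialogue, and no matching exclusion covers earlier crisis care under TAU.

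Section 3 (Intervention delivery) states: "Open Dialogue is not offered to those in the TAU arm". Section 4.2.1 places the baseline crisis referral in the sequence: "This referral takes place after cluster randomisation, but before a potential participant has been assessed as meeting eligibility criteria prior to consent".

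On timing, section 2.2 says: "Participant recruitment commenced in the first site in June 2019, and all other sites were able to open to recruitment by January 2020". It adds "Recruitment was suspended in March 2020", and that recruitment was "restarted across the six sites from August 2020 to December 2020". Section 5.1 reports that both services moved quickly to remote working when the pandemic began, so care continued while enrolment did not.

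The primary Cox model in section 2.6 contains arm, catchment area, list size and deprivation. It has no patient-level history. Service use in the six months before the index crisis is extracted from records (section 2.5 and Table 2), but it is not in that model.

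**The concern.** An exclusion applied after randomisation is harmless only if it removes comparable people from both arms. Here, whether a person has ever had Open Dialogue depends largely on the cluster in which they are registered, so eligibility depends on allocation. No recruiter preference is needed for this to happen.

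Take one person who has a crisis during the recruitment pause, or who declines the research, and who returns in crisis a year later while recruitment is open. In an Open Dialogue cluster the earlier episode was treated with Open Dialogue, so the person is ineligible. In a TAU cluster the same person is eligible.

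If such returners relapse sooner after recovery than others, the TAU arm carries a higher-risk group that the Open Dialogue arm lacks. The primary hazard ratio would then fall below 1 with no treatment effect. Intention-to-treat analysis cannot restore people who were never enrolled, and blinded outcome rating does not affect who enters.

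**Working it through.** **1. The plan's own figures (section 2.5.1).** Freedman's formula, two-sided 5%, 90% power, hazard ratio 0.589: (1.960 + 1.282)² × (1.589/0.411)² = 157.06, stated as 157. Design effect: 1 + 17 × 0.04 = 1.68. 157 × 1.68 = 263.8, stated as 264. 264/0.49 = 538.8, stated as 538. The figures reproduce to within rounding. The effective information used below is 264/1.68 = 157 events.

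**2. How many people could be treated but not enrolled.** Inputs: 65 to 75 crisis referrals per cluster per year (section 2.3), 19 recruits per cluster (section 2.5.1), and the dates in section 2.2.

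- Pause: 5 months (March to August 2020) to 9 months (March to December 2020). 65 × 5/12 = 27 to 75 × 9/12 = 56 referrals per cluster. Over 15 Open Dialogue clusters (assuming 30 split equally), about 410 to 840.
- Open recruitment: shortest 2 + 12 = 14 months (opened January 2020, restarted December 2020); longest 9 + 16 = 25 months (opened June 2019, restarted August 2020). 65 × 14/12 = 76 to 75 × 25/12 = 156 referrals per cluster. 19/76 = 25% and 19/156 = 12%, so roughly 75% to 88% of referrals were not enrolled.

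These are referrals, not distinct treated people. Some are repeats, some are ineligible in either arm, and the pause figures assume that referral rates held in the pandemic. They show that the pool is not trivial; they do not give the share who return.

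**3. What a given share would do.** Let f be the share of TAU participants who are such returners and k their relapse hazard relative to the rest. Both are assumptions. Set f = 0 in the Open Dialogue arm, no true effect, exponential hazards, and 49% relapse in TAU at 24 months. The base hazard λ over 24 months solves

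(1 − f)(1 − e^(−λ)) + f(1 − e^(−kλ)) = 0.49.

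The apparent hazard ratio is the large-sample Cox estimate comparing this mixture with a single exponential of hazard λ. Example, f = 20%, k = 2: λ = 0.58, so Open Dialogue relapse is 44.1%; check for TAU: 0.8 × 0.441 + 0.2 × 0.688 = 0.49. The Cox estimate is 0.86.

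For the false-positive rate, the standard error is 2/√157 = 0.160. With |ln 0.86| = 0.151, the shift is 0.94 standard errors, and the two-sided rejection probability is Φ(0.94 − 1.96) + Φ(−0.94 − 1.96) = 15.7%.

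| f | k = 1.5 | k = 2 | k = 3 |
|---|---|---|---|
| 5% | 0.98 (5.2%) | 0.96 (5.6%) | 0.94 (6.6%) |
| 10% | 0.96 (5.8%) | 0.93 (7.6%) | 0.89 (11.7%) |
| 20% | 0.92 (8.4%) | 0.86 (15.7%) | 0.78 (33.3%) |

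Entries are the apparent hazard ratio, with the two-sided type I error (nominal 5%) in brackets. At k = 1 there is no bias. At k = 0.8 it reverses: 1.01, 1.02 and 1.04 for f = 5%, 10% and 20%.

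Against the target, ln 0.589 = −0.529. The mildest cell (0.979 before rounding) is 0.021/0.529 = 4% of the target log hazard ratio, and the most severe (0.784) is 0.243/0.529 = 46%.

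The model starts everyone at risk at time zero. The real outcome runs from recovery, so the relevant f and k are those among people who recover.

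**The case against.** The strongest case on the other side is that the asymmetry is clear but its consequence is not. Four points stand.

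- A reader might infer that the criterion can act only in Open Dialogue clusters. The documents do not show that. The programme included a feasibility trial (section 2), and people change practice, so someone in a TAU cluster could also have had Open Dialogue. Section 3.1 says "All Open Dialogue and TAU teams are monitored prior to participant recruitment and at 6-monthly intervals throughout intervention delivery", which suggests Open Dialogue was being delivered before sites opened, but not which practices those early patients came from. The routes that are well supported are the pause and people treated but not enrolled.
- A reader might infer that repeat-crisis patients in general are removed from one arm. Only those whose earlier episode was under an Open Dialogue team are removed. People whose earlier crises came before that team opened remain eligible in both arms.
- A reader might take bias towards Open Dialogue as established. No section gives the relapse risk of returners, and none gives their share. People who decline once may decline again, which would keep the share small, and at 5% the shift is small.
- Dropping participants from the primary analysis would sit badly with the intention-to-treat commitment in section 2.6.2 and with the stated aim in section 6 of keeping exclusions few.

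It can also be said that recent service use is already collected and that further analyses are left to an analysis plan not shown here. That helps only in part. The extraction reaches back six months while the exclusion is unlimited, and the primary model that the article does specify omits these data. The criterion itself is fixed in the protocol and is not a matter for the analysis plan.

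**Conclusion.** The point holds in a limited form. The exclusion is applied after allocation, works almost entirely in Open Dialogue clusters, has no TAU counterpart, and is not offset by the stated primary model. It could bias the primary hazard ratio, plausibly towards Open Dialogue.

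The size cannot be fixed from the documents. The range of about 0.98 to 0.78 rests on assumed shares of 5% to 20%, assumed relative hazards of 1.5 to 3, exponential times, and no such returners in the Open Dialogue arm. At the low end the effect on the conclusion would be slight; at the high end it would be nearly half the target effect on the log scale. A firmer statement that the result will favour Open Dialogue is not supported, because the bias vanishes if returners carry the same risk and reverses if they carry less.

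This should be corrected, since it bears on the headline result and the remedy is cheap. It is not a fault that invalidates the design.

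**What to change.** 1. Keep the intention-to-treat Cox model as primary, and add to it the crisis referrals and service use in the six months before baseline. These are already extracted. This addresses imbalance in recent history only.
2. Pre-specify a key sensitivity analysis that removes, from both arms, anyone with a crisis episode under the participating service since the date the local Open Dialogue team began accepting patients. TAU clusters use the date for the team in their own catchment area. A person's first episode after that date precedes any exposure to that team, so this selection cannot depend on arm in the way the present rule does.
3. Report by arm the number screened out for earlier Open Dialogue. Report also how many TAU participants the look-back in item 2 identifies, which gives a direct estimate of f.
4. Apply the same symmetric look-back to any recruitment still to come.

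The cost is one longer look-back in records already accessed, a few lines in the protocol and analysis plan, and the loss of some TAU participants and events in the sensitivity analysis. Section 4.3 has the analysis plan signed off before database lock and section 2.2 puts analysis in early 2024, so items 1 to 3 remain possible after enrolment has closed.
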